### Material management

Questionnaires are stored in a locked-up room and closet at the Folkhälsan Research Center. Data is transferred into a digital format and analyzed anonymously using an identification number given for each participant, not allowing for personal identification, and is managed by designated, trained personnel. Only selected members of the research group have access to the data.

## Analysis plan

Data will be analyzed on an intention to treat basis including all randomized classes in the groups to which they were randomly assigned. Descriptive statistics (mean, median or percentages as appropriate) will be used to summarize the baseline characteristics and outcomes in each group.

Statistical analysis will be done with multilevel (hierarcial) models to account for the clustering within schools. Continuous outcomes will be analysed with linear mixed effects models and categorical outcomes with generalized linear mixed effects models. Maximum likelihood estimation will be used to get unbiased and efficient parameter estimates for data with missing values in the follow-up measurements.

The effectiveness of the mindfulness intervention on primary and secondary outcomes will be first analyzed using unadjusted analyses and then adjusted for age, sex and baseline values of the outcomes. The modifying effect of factors (i.e. sex, childen’s age, health status, circumstances at home, social relationships, hobbies, school achievement) on the effectiveness of mindfulness will be analysed using tests of interactions. Interaction analyses are exploratory in nature. The differences in the continuous outcomes between groups will be presented using mean differences with 95 % confidence intervals. Results are expressed using odd ratios with 95 % confidence intervals for categorical outcomes. Two-sided statistical tests with a 5 % level of significance will be used.

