### Randomization procedure

The recruitment started by listing all the schools in a Southern part of Finland. After choosing the schools (including as many classes of the same grade as possible), a letter explaining the study procedure was sent by e-mail to the head masters. Within few days after sending the information letter, the research team members called the headmasters by telephone. In most schools the decision to take part to the study was made collectively by the head master and the class teachers (of the chosen grades). The schools were enrolled from 14 cities/municipalities during the collection of the data (years 2014–2016). Altogether 247 schools were contacted, 59 of those participated in the study participation percentage being 24. In each municipality we aimed at an equal number of intervention and control classes. In order to achieve balanced intervention and control groups, schools participating in the study were randomized using the available background variables. The selection of intervention-control pairs was primarily based on the language being used for teaching (Finnish, Swedish or English, the grade, the school location, the number of classes participating in the investigation and, if necessary, the average apartment price per square meter in the school’s neighborhood).

The classes were randomly assigned to mindfulness intervention classes (*N* = 85) and control classes (*N* = 79) and non-treatment classes (*N* = 28). Due to practical reasons, in spring 2014 and in autumn 2015 schools were divided into two arms (intervention and control) and in spring 2015 and spring 2016 into three arms instead of two: intervention, control and non-treatment groups. First, the schools were divided into three groups based on the school location and the average apartment price per square meter. Within each of these groups, the total number of schools and classes varied. Next, the schools for these groups were divided into three subgroups including approximately same number of classes (some schools were combined into one subgroup to achieve an as even distribution of classes as possible).

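### Neither planned model contains the factors used to allocate schools or the recruitment term: some precision is lost against active control, and term is mixed with arm against non-treatment

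*Protocol article*

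**What the plan says.** Under Randomization procedure, the article describes restricted allocation. For the two-arm terms, "The selection of intervention-control pairs was primarily based on the language being used for teaching", and the other pairing factors are "the grade, the school location, the number of classes participating in the investigation and, if necessary, the average apartment price per square meter". Balance within municipality is stated as an intention: "In each municipality we aimed at an equal number of intervention and control classes". Schools were split "in spring 2015 and spring 2016 into three arms instead of two"; there, "the schools were divided into three groups based on the school location and the average apartment price per square meter", and each group was then cut into three subgroups with similar numbers of classes, some schools being combined.

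Under Analysis plan, outcomes are analysed without adjustment and "then adjusted for age, sex and baseline values of the outcomes", in multilevel models whose only stated clustering is within schools. The plan does not say which of the two models decides the result.

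Under Data collection timeline, intervention and control students were enrolled in four terms (523, 1090, 821 and 203). Non-treatment students were enrolled only in spring 2015 (254) and spring 2016 (109).

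**The concern.** When allocation is balanced on factors that predict the outcome and the model leaves them out, their variance stays in the school-level error term. The actual sampling variance of the arm difference is smaller because of the balance, but the reported standard error does not show it. Intervals are then too wide and the test too strict.

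The non-treatment comparison has a different problem. That arm exists in only some terms. A model that pools all terms without a term effect sets intervention students from every term against non-treatment students from two terms, so any difference between terms enters the estimate.

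The statistical analysis plan is not available, but this is not a detail left to it: the article names its covariates, and the design factors are not among them.

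**Working it through.** **Inputs from Sample size.** Difference 0.2 SD, 80% power, two-sided 5%, ICC 0.03, 60 completing children per school.

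**Reproducing the stated figure.** A two-mean comparison at 0.2 SD needs 393 per group. The design effect is 1 + 59 × 0.03 = 2.77, and 393 × 2.77 = 1089, against 1090 stated. The sample size is not in dispute.

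**Share of variance that matching can act on.** Per child, the between-school part of 2.77 is 60 × 0.03 = 1.8, and 1.8 / 2.77 = 65%.

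**Effect of leaving the factors out.** Let R² be the share of between-school variance that the allocation factors explain. The article gives no value, so R² is assumed.
- Reported SE, factors ignored: √(2 × 2.77 / 1090) = 0.0713 SD.
- True SE under balanced allocation: √(2 × (2.77 − 1.8 R²) / 1090).
- Type I error of the planned test: 2 × [1 − Φ(1.96 × 0.0713 / true SE)].
- Power, ignored: Φ((0.2 − 1.96 × 0.0713) / true SE). Power, included: Φ(0.2 / true SE − 1.96).

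| R² (assumed) | True SE | SE too wide by | Type I error | Power ignored | Power included |
|---|---|---|---|---|---|
| 0 | 0.0713 | 0% | 5.0% | 80% | 80% |
| 0.2 | 0.0665 | 7% | 3.6% | 82% | 85% |
| 0.5 | 0.0586 | 22% | 1.7% | 85% | 93% |

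These figures are for a model without covariates.

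**Simulation check.** 1090 / 60 gives about 18 schools per arm. With 18 matched pairs of school means, t-tests and 40,000 runs per scenario:
- R² = 0.25: type I error 3.3% ignored, 4.9% paired; power 79% and 82%.
- R² = 0.5: type I error 1.9% ignored, 4.9% paired; power 81% and 89%.
- R² = 0: power 77% ignored, 75% paired. Pairing that explains nothing costs about 2 points.

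**Non-treatment contrast.** Intervention and control students total 523 + 1090 + 821 + 203 = 2637. The two terms without a non-treatment arm supply 523 + 1090 = 1613, and 1613 / 2637 = 61%. Non-treatment students total 254 + 109 = 363. Assume that the intervention arm follows the same split by term and that outcomes in the terms without that arm differ by 0.1 SD from the others. The unadjusted contrast then shifts by 0.61 × 0.1 = 0.06 SD, one fifth of the 0.3 SD targeted for this comparison. The shift can go either way.

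**The case against.** **The loss may be small.** R² is assumed. The Background section describes Finnish schools as homogeneous, with school-related variance minimized and areal segregation still rather low, which points to the low end. The adjusted model already holds the baseline outcome, which absorbs stable school differences, and age, which tracks grade. This stands: the tabulated figures apply at most to the unadjusted model.

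**Omitting pairs is valid, only less efficient.** This stands for mindfulness versus relaxation. The error rate falls below 5%, and the estimate is not biased.

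**The factors must not be overstated.** Municipality balance was an aim, and term is implied by term-wise allocation without being listed as a pairing factor. Three-arm terms used groups and subgroups, not pairs, so one pair intercept is not defined throughout. This also stands and shapes the fix.

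**Stronger readings that a reader might infer.**
- That the primary contrast is confounded by term. The article has both arms recruited together in every term, so it does not support this.
- That modelling the factors lifts power from 80% to between 85% and 93%. Balanced allocation also reduces the true variance under the planned test, so the fair starting point is 82% to 85%.
- That listing the unadjusted analysis first makes it primary. The wording gives a sequence and no ranking.

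None of this removes the mismatch between allocation and model, or the term problem in the non-treatment contrast.

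**Conclusion.** The point holds, with two different consequences.

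For mindfulness versus relaxation, the analysis is conservative and somewhat inefficient. In the unadjusted model, at an assumed R² of 20% to 50%, about 3 to 8 points of power are given up. The adjusted model gives up less, by an amount that cannot be derived from the article, and nothing is lost at R² = 0. The calculation treats the school as the unit, as the article's own sample size does.

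For mindfulness versus non-treatment, there is possible bias in either direction, because 61% of intervention and control students come from terms without that arm. Baseline adjustment reduces it; the unadjusted model has no such protection. The article says that this comparison was not its primary interest, which limits the weight of the problem.

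The change is advisable but not essential to the validity of the main comparison.

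**What to change.** 1. Name the adjusted model as primary and report the unadjusted model as supportive.
2. To baseline value, age and sex, add recruitment term and the allocation factors as fixed effects: teaching language, grade, location/price group and number of classes. Alternatively, use a random intercept for the pair or block in the terms where one is defined.
3. For the non-treatment contrast, adjust for term or restrict the comparison to terms that included that arm. Restriction drops the 1613 intervention and control students from the other terms, so adjustment keeps more data.
4. Reconcile the terms before coding them: Randomization procedure names autumn 2015 as a two-arm term, while Data collection timeline lists autumn 2014 and no autumn 2015.

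**Cost.** This is a change of wording in the analysis plan. The factors were used for allocation, so no new data collection should be needed. Some between-school degrees of freedom are spent. With 18 full pairs they fall from 34 to 17, which costs about 2 points of power if the factors explain nothing.

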## Discussion

This paper describes the rationale and design of a cluster randomized controlled trial of a mindfulness intervention program among children and adolescents compared to an active control group receiving standard relaxation program, and a non-treatment group. The trial presented in this protocol aims to expand our knowledge on the effectiveness of mindfulness on a variety of behavioral, emotional, cognitive, and psychophysiological outcomes, compared to an alternative treatment and no treatment at all.

By testing the effectiveness of two alternative strategies for promoting human resilience and well-being, the present research will eventually offer new insight into the comparative usefulness of mindfulness interventions. We also focus on the unresolved questions of the mindfulness research by using a systematic and sound design to avoid methodological shortcomings.

To our knowledge, the present study is among the first ones to conduct systematic, methodologically rigorous comparative randomized research among school-aged children, on the effects of mindfulness on mental well-being.

## Abbreviations

No abbreviations used.
